**Table 1 T1:**
[figure not shown]
Scores for symptoms and signs.

### Sample size calculation

2.6

According to the response rates of treatment, the cohort 1 and the cohort 2 were 53% and 40%, respectively. It was estimated that 250 patients of each group would be sufficient to achieve 90% power in detecting treatment differences, based on a 2-sided alpha at a significance level of 0.05. Meanwhile, considering a dropout rate of 20%, we concluded that a total of 300 patients for each cohort would need to be recruited to ensure significant results.

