### Study design

2.1

This large, prospective, multicenter cohort study is being conducted in 3 institutions between May 2015 and May 2020. Six hundred participants are recruited and divided into 2 cohorts, with 300 individuals per cohort. All cohorts will undergo a 12-week treatment and a 12-month follow-up period. Participants will be asked to visit the clinicians every 2 weeks during the treatment period and once a month during the follow-up period. The feasibility and preciseness of the whole process are supervised by 1 to 2 supervisors.

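### 250 per group gives about 83% power at two-sided 0.05, not the stated 90%, and the 20% dropout allowance leaves only 240

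*Protocol article*

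**What the plan says.** Section 2.6 (Sample size calculation) gives every input needed to check the result. On the assumed response rates: "the cohort 1 and the cohort 2 were 53% and 40%, respectively". On the size before dropout: "It was estimated that 250 patients of each group would be sufficient to achieve 90% power in detecting treatment differences". On the test: "based on a 2-sided alpha at a significance level of 0.05". On attrition: "considering a dropout rate of 20%, we concluded that a total of 300 patients for each cohort would need to be recruited".

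Section 2.1 (Study design) repeats the recruitment target with equal cohorts: "Six hundred participants are recruited and divided into 2 cohorts, with 300 individuals per cohort".

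**The concern.** A 13-point difference near 50%, tested two-sided at 0.05 with 90% power, usually needs about 300 evaluable patients per group, so 250 looked too small. The dropout step also looked wrong. Going from 250 to 300 adds 20% of the smaller number, whereas a 20% dropout rate removes 20% of the larger one.

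The stated power is what readers will use to judge a non-significant result. If the true type II error is well above 10%, failing to find a difference is weaker evidence against Chinese herbal medicine than section 2.6 implies.

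**Working it through.** **Inputs** (section 2.6; equal cohorts from section 2.1): p1 = 0.53, p2 = 0.40, difference d = 0.13, alpha 0.05 two-sided, power 90%, 250 per group before dropout, dropout 20%, 300 recruited per cohort.

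**Formula** (two proportions, 1:1, pooled variance under the null):

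n = [z_α √(2p̄(1−p̄)) + z_β √(p1(1−p1) + p2(1−p2))]² / d²

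- p̄ = (0.53 + 0.40)/2 = 0.465
- √(2 × 0.465 × 0.535) = √0.49755 = 0.7054
- √(0.2491 + 0.2400) = √0.4891 = 0.6994
- z_β = 1.2816 for 90% power

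**Step 1: trying to reproduce 250.**

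- Two-sided 0.05 (z_α = 1.9600): (1.3825 + 0.8963)² / 0.0169 = 307.3, so 308 per group.
- One-sided 0.05 (z_α = 1.6449): (1.1602 + 0.8963)² / 0.0169 = 250.2.

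Other two-sided formulas at 90% power do not give 250 either: unpooled 304.1, arcsine 307.6, continuity-corrected 323. At the stated 90% power, only a one-sided test gives a figure of 250.

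**Step 2: power at the relevant sizes**, two-sided 0.05, from power = Φ[(d√n − 1.9600 × 0.7054) / 0.6994]:

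| n per group | d√n | z | Power |
|---|---|---|---|
| 240 (300 less 20%) | 2.0140 | 0.903 | 81.7% |
| 250 (stated) | 2.0555 | 0.962 | 83.2% |
| 300 (all recruited) | 2.2517 | 1.243 | 89.3% |
| 308 | 2.2815 | 1.285 | 90.1% |

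The exact binomial power of the pooled z-test is 84.0% at 250 and 81.5% at 240, so the gap does not come from the normal approximation. With a continuity correction, power at 250 is lower still, at 80.8%.

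**Step 3: the dropout allowance.**

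- The plan's step: 250 × 1.20 = 300.
- What remains after 20% loss: 300 × 0.80 = 240, which is 10 short of 250.
- Needed to keep 250: 250 / 0.80 = 312.5, so 313.
- Needed to keep 308: 308 / 0.80 = 385 per cohort, 770 in total, against 600 planned.

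**Step 4: size of each error.** The shortfall at 250 costs about 7 points of power (90% to 83.2%). The dropout step costs a further 1.5 points (83.2% to 81.7%). Type II error at 240 is 1 − 0.817 = 18.3%, against 10% stated. With 240 per group, 90% power is reached only for a difference of about 14.7 points (54.7% against 40%).

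**The case against.** The strongest objection concerns who is analysed. Section 2.9 fills missing data by last observation carried forward. If that covers the response endpoint, patients who drop out after at least one assessment stay in the analysis, the analysed number approaches 300, and nominal power is 89.3%, within a point of 90%. On that reading 82% is the lower end of a range. This stands as far as it goes, and the restated power should say which patients it refers to. It does not rescue section 2.6, which attributes 90% to 250 patients and itself treats the 20% as lost. Even 300 falls slightly short of 90%, and carried-forward values add no information about the true later outcomes of those patients.

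Second, the document never mentions a one-sided test. The match at 250.2 is close but circumstantial: a two-sided calculation at 80% power with continuity correction gives 246, also near 250. The one-sided origin is therefore likely, not proven. The stated combination of size, power and sidedness is wrong under either explanation.

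Third, the study is presented as a basis for later confirmatory work and recruitment may be complete, so the number may no longer be changeable. That is a reason to correct the statement rather than the sample size, not a reason to leave it.

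**Conclusion.** The concern holds. For 53% against 40% at two-sided 0.05, 250 per group gives about 83% power, and 90% needs 308 evaluable per group. After the plan's own 20% loss, 240 remain and power is about 82%; with no loss at all, 300 give 89.3%. The probability of missing the planned 13-point difference is about 18% if only the 240 are evaluable, nearly twice the stated 10%. The mismatch between 250 and a two-sided test is the main error, and the dropout inflation is a lesser one.

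This rests on reading the response rate as a binary endpoint compared between two equal groups without covariate adjustment, as section 2.6 implies. No figure from outside the document was used.

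**What to change.** Keep 300 per cohort and rewrite section 2.6, for example: *With 300 recruited per cohort and 20% dropout (240 evaluable), power is about 82% to detect 53% versus 40% at a two-sided alpha of 0.05. If all 300 are analysed, power is about 89%. Power of 90% would require 308 evaluable patients per cohort.*

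State the dropout inflation as n/(1 − 0.20). Remove the closing suggestion that the sample size secures a significant result, since no sample size can do that.

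The cost is one paragraph and a less favourable power figure. No extra patients are needed, but only because this version gives up the 90% target. Keeping 90% with 20% dropout would mean 385 per cohort, 770 in total, which is 170 more than planned.

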### Safety assessment

2.7

For the sake of participant safety, the following biological indicators will be monitored and watched throughout the trial: blood routine, liver function (AST, ALT), renal function (BUN, Cr), and electrocardiography (ECG). Any unexpected symptoms and signs or feelings of discomfort in patients will be recorded as adverse events. For each adverse event, the starting date, ending date, degree, relationship to the trial and potential to trigger patient drop-out from the study will be carefully recorded and considered. If an adverse event occurs, the patient will be monitored until his/her adverse event disappears.

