## Introduction

1

Henoch–Schönlein purpura (HSP) is a systemic disorder characterized by leukocytoclastic vasculitis involving the capillaries and deposition of IgA immune complexes.^[1]^ The ages of more than 90% of HSP patients are <10 years.^[2,3]^ Epidemiological studies have shown that Asians have a relatively higher incidence rate of HSP than Caucasians and Africans.^[2]^ Kidney injury, which is called Henoch–Schönlein purpura nephritis (HSPN), is one of the major manifestations and the primary cause of mortality from HSP.^[1]^ During the 4 to 6 weeks of initial disease presentation, approximately 40% of children with HSP progress to HSPN.^[4,5]^ Persistent purpura, severe abdominal symptoms, and an older age are 3 of the strongest risk factors for HSPN.^[6]^ Great efforts are needed to control the kidney injury for children with HSP who are at an increased risk of renal insufficiency.

However, therapies of Western medicine (WM) for HSPN, including corticosteroids, immunosuppressive treatment, and anticoagulant therapy, have the potential to cause adverse side effects and remain controversial.^[7–9]^ A clinical study demonstrated that early corticosteroid therapy does not prevent delayed nephritis in children with HSP.^[10]^ Immunosuppressive agents including cyclophosphamide have side effects such as oncogenesis, myelosuppression, hemorrhagic cystitis, and interstitial pneumonia.^[11,12]^ Moreover, the symptoms may recur easily after a long duration of treatment. Effective treatment for improving the long-term clinical management of HSPN remains an urgent need.

In China, the majority of HSPN patients resort to Chinese herbal medicine (CHM), acupuncture, and other traditional Chinese medicine (TCM) therapies.^[13,14]^ In TCM, HSPN is categorized as “purpura” or “hematuria.” In recent years, quite a few trials conducted in China have suggested that the use of CHM in conjunction with corticosteroids or immunosuppressive drugs generated additional positive effects,^[15–20]^ such as relieved blood hypercoagulable state, reduced proteinuria, and improved TCM signs and symptoms. These results indicated a potential role for CHM in the combined, consolidate, and maintenance treatment of HSPN. In this trial, we intend to assess the efficacy and advantage of the use of CHM for the treatment of children with HSPN.

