### Study settings and participants

2.2

HSPN patients are being recruited from outpatient and inpatient departments of three large comprehensive hospitals in China, including the Affiliated Hospital of Liaoning University of TCM, the First Affiliated Hospital of China Medical University, and the Shengjing Hospital of China Medical University. The patient screening will be conducted by clinicians who are not involved in the study. If a patient meets the study criteria, the clinician who is responsible for the patient screening will provide him/her with written information, explain the study in detail in an understandable language and obtain the written consent if he/she is willing to take part in the study. Informed consent must be obtained for all patients enrolled in the study. The eligible children with HSPN taking CHM in one of the above 3 hospitals were classified as cohort 1 and participants received WM without CHM belong to cohort 2. Trials that combine CHM with WM will be included, if the cohort 2 received the same WM as the cohort 1. Doctors of traditional Chinese medicine in the above hospitals prescribe CHM for patients according to their symptoms and signs, tongue manifestations, and pulse condition. The study flow chart is shown in Figure 1.

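### Section 2.7 qualifies recordable symptoms and signs as unexpected and rates causality against the trial, so known, unfelt Western medicine effects can be missed and single events cannot be assigned to one treatment

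*Protocol article*

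**What the plan says.** Section 2.7 (Safety assessment) gives the article's only definition of an adverse event: "Any unexpected symptoms and signs or feelings of discomfort in patients will be recorded as adverse events". It then lists what is noted for each event: "the starting date, ending date, degree, relationship to the trial and potential to trigger patient drop-out from the study will be carefully recorded". The same section has routine blood tests, liver enzymes, urea, creatinine and ECG monitored throughout, but does not say whether an abnormal result becomes an adverse event.

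Four other places bear on this:

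- **Section 1 (Introduction)** states: "Immunosuppressive agents including cyclophosphamide have side effects such as oncogenesis, myelosuppression, hemorrhagic cystitis, and interstitial pneumonia". Side effects of WM are part of the stated reason for the study.
- **Section 2.2 (Study settings and participants)** puts children taking CHM in cohort 1 and says that "participants received WM without CHM belong to cohort 2". It also allows combined treatment: "Trials that combine CHM with WM will be included, if the cohort 2 received the same WM as the cohort 1".
- **Section 2.5.2 (Secondary outcomes)** lists adverse events as a secondary outcome.
- **Section 2.9 (Statistical analysis)** bases the safety assessment on compliance and adverse events.

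**The concern.** An adverse event record normally takes in every untoward event and leaves the question of whether it was expected to a later step. Here the word *unexpected* sits in the capture rule itself. The Introduction describes some WM effects as known, so a clinician who follows section 2.7 to the letter has grounds to leave a sign of one of them unrecorded.

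This matters because the article's closing hypothesis is that CHM is effective and safe, and the case against WM in the Introduction rests partly on its side effects. A filter on known effects acts on the events by which the safety of the two cohorts would be compared. An event never entered on the case report form cannot be restored in the analysis.

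The causality item raises a second, independent question. Doctors prescribe the treatment in ordinary care, and the study assigns none. Relationship to the trial is therefore not relationship to a treatment, and some children may receive two kinds of treatment.

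**Working it through.** The plan states no safety figure, so there is none to reproduce. The check is a comparison of texts, followed by an illustration of the possible range.

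**1. What the capture rule lets through.** The sentence has two limbs: symptoms and signs, qualified as unexpected, and feelings of discomfort. On the reading kinder to the plan, *unexpected* qualifies only the first limb. An event is then recorded if it is unexpected or if the child feels it. What can be lost is an event that is both expected and unfelt.

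**2. Applying this to the effects the article names.** Haemorrhagic cystitis and interstitial pneumonia would ordinarily be felt and so would enter by the second limb. Myelosuppression should show in the scheduled blood tests, though the text does not say that the result then counts as an adverse event. The Introduction offers its list as examples, so other known, unfelt signs fall under the same rule. The gap is real but narrower than the whole list.

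**3. Who is exposed to the loss.**

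| Group (section 2.2) | On WM | Known WM effects can be lost |
|---|---|---|
| Cohort 1, CHM alone | no | no |
| Cohort 1, CHM plus WM | yes | yes |
| Cohort 2, WM without CHM | yes | yes |

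The loss is unequal only to the extent that cohort 1 children take CHM alone. Where it is unequal, cohort 2 loses more, and the comparison would tend to make WM look safer than it is.

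**4. Range of the effect.** Let *r* be a true event rate common to both cohorts, *f* the fraction of events lost in children on WM, and *w* the share of cohort 1 on the same WM. Recorded rates are *r*(1 − *f*) in cohort 2 and *r*(1 − *fw*) in cohort 1. The false difference is *rf*(1 − *w*). The article gives none of *r*, *f* or *w*. The values below are assumptions; only the 300 per cohort is the plan's (section 2.1). With *r* = 20%, there are truly 60 events in each cohort.

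- *w* = 1, any *f*: the difference is 0. For *f* = 0.5, the counts are 30 and 30.
- *w* = 0, *f* = 0.25: 45 in cohort 2 against 60 in cohort 1, or 15% against 20%. Pooled rate = 105/600 = 0.175; SE = √(0.175 × 0.825 × 2/300) = 0.0310; z = 0.05/0.0310 = 1.61; two-sided p about 0.11.
- *w* = 0, *f* = 0.5: 30 against 60, or 10% against 20%. Pooled rate = 90/600 = 0.15; SE = √(0.15 × 0.85 × 2/300) = 0.0292; z = 0.10/0.0292 = 3.43; two-sided p about 0.0006.

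The last line is an extreme case: half of cohort 2's events are lost and none of cohort 1's. It shows what the rule could do at worst under these assumptions and is not an estimate.

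**5. The causality item.** For a child on CHM alone or WM alone, relationship to the trial might be read as relationship to the one treatment taken. For a child on both, it gives one answer where two are needed. This holds however *unexpected* is read.

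**The case against.** The strongest reply is that *unexpected* may be loose English for untoward. The article has other slips of language, nothing in it tells a site to check an event against a list of known effects before recording it, and sections 2.5.2 and 2.9 speak of adverse events without such a limit. This may well be what was meant. But section 2.7 is the only place where the term is defined, and no other text widens it.

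A second reply is that the article condenses a full protocol and a case report form that are not shown. That would answer a complaint about missing detail. Here the wording is present, for both capture and causality, and it is the wording that is in question. The fuller documents may still differ, which limits confidence.

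A reader might infer three stronger things that the article does not support:

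- *That only unexpected events count.* The word only does not appear, and the discomfort limb admits known effects that the child feels.
- *That nearly every event on CHM would be recorded while WM events are dropped.* The article lists no expected effects for CHM, but it does not say how sites would treat CHM events. It also does not say how many children receive cyclophosphamide or corticosteroids. Cohort 1 children on the same WM would lose the same events.
- *That harm cannot be attributed to CHM or WM at all.* Event rates can still be compared between cohorts, and between CHM plus WM and the same WM alone, subject to confounding because treatment is not randomised. What is absent is attribution of the single event.

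**Conclusion.** The point holds as a defect of stated wording. Taken literally, section 2.7 permits a site to leave out an expected sign of a known WM effect that causes no discomfort. The loss may be greater in cohort 2, and if so it would tend to understate WM harm. That conclusion rests on the literal reading of *unexpected* and on some cohort 1 children taking CHM alone. The amount cannot be estimated from the documents and could be nil.

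The causality entry does not separate CHM from WM at event level for a child taking both. That part depends on neither assumption.

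Both parts should be put right because adverse events are a secondary outcome and a basis of the safety assessment. Neither makes the cohort comparison of event rates impossible. Confidence is moderate, since the full protocol may word these items differently.

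**What to change.** In section 2.7, and in the case report form if it carries the same wording:

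1. Delete *unexpected*. Record every new or worsening untoward sign, symptom or discomfort in both cohorts, whether or not it is a known effect of the treatment.
2. Replace the single entry "relationship to the trial and potential to trigger patient drop-out from the study" by separate entries for relationship to CHM and relationship to WM, and keep the drop-out item as its own field.

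The cost is one reworded sentence and one divided field. Sites will have somewhat more events to record, at visits that are already scheduled. The change affects recording only and leaves clinical management as it is. If data have already been collected under the present wording, events left out may not be recoverable, and the report should state which rule was in force when they were recorded.

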### Data collection

2.8

Both cohorts undergo a 12-week treatment and 12-month follow-up. Case report forms (CRFs) contain a range of information, and these will be completed by the corresponding researchers at each center. The recruited patients will be asked to visit the clinicians 7 times for the assessment of the treatment efficacy during the treatment period (at baseline and in the 2nd, 4th, 6th, 8th, 10th, and 12th weeks after the first treatment). During the follow-up period, patients will be asked to visit once a month. If a patient fails to visit during one of the follow-up observations, the assessor will contact him/her by phone (Table 2). All data collected using paper-based CRFs will be submitted to an online clinical research data-capture computer system developed by the research group (http://59.46.50.9:9889). Only the members from the research team will have access to these data.

**Table 2 T2:**
[figure not shown]
Calendar summary.

### Statistical analysis

2.9

The statistical analysis will be conducted by a statistician of the Institute of Basic Research in Clinical Medicine, China Academy of Chinese Medical Sciences, Beijing, China. The statistician is blinded to the entire trial and will use SAS 9.1.3 (SAS Institute, Cary, NC, USA) and SPSS Version 13.0 (SPSS Inc., Chicago, IL) software. To test the hypotheses about associations between baseline risk factors and HSPN incidence, hazards ratios will be computed using the Cox proportional hazard regression models. Baseline differences between the groups will be assessed with the use of Student's *t*-test for normally distributed continuous variables and the nonparametric Mann–Whitney *U*-test for non-normally distributed variables. Comparisons between the groups will be conducted using an analysis of covariance (ANCOVA) with the baseline as the covariate. For efficacy analysis, changes from the baseline to the endpoint of treatment in scores will be tested with repeated measured analysis of variance (ANOVA). Within each group, differences will be assessed with paired t-test for normally distributed data and the Wilcoxon signed-rank test for non-normally distributed data. Safety will be assessed by participant compliance and adverse events. For analysis of the final dataset, missing data will be filled in using the last observation carried forward (LOCF) approach. A *P* value <.05 is considered significant.

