**Methods and analysis::**

This large, prospective, multicenter cohort study started in May 2015 in Shenyang. Six hundred children diagnosed with HSPN were recruited from 3 institutions and are followed-up every 2 to 4 weeks till May 2020. Detailed information of participants includes general information, history of treatment, physical examination, and symptoms of TCM is taken face-to-face at baseline.

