#### Inclusion criteria

2.4.2

1.A diagnosis of HSPN according to the diagnosis criteria.2.Age: 5 to 18 years old (including 5 and 18 year old).3.The clinical classification of HSPN includes isolated hematuria, insolated proteinuria, hematuria with proteinuria, and acute glomerulonephritis.4.The ability to provide detailed connection and complete a follow-up.5.The ability to understand and sign a written informed consent.

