#### Primary outcomes

2.5.1

The primary outcomes of this study are remission rate and recurrence rate of HSPN.

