#### Secondary outcomes

2.5.2

1.Symptom improvement (such as urine erythrocyte, urine protein, etc)2.Adverse events.

Each symptom or sign will be given a score, and the sum of all scores will be recorded in Table 1.

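### Section 2.9 applies its Cox model to onset of a disease every child already has, and ties no suitable adjusted CHM versus WM comparison to remission or recurrence

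*Protocol article*

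**What the plan says.** - **Population.** The first inclusion criterion (section 2.4.2) is "A diagnosis of HSPN according to the diagnosis criteria". The abstract agrees: "Six hundred children diagnosed with HSPN were recruited from 3 institutions".
- **Primary outcomes (section 2.5.1).** "The primary outcomes of this study are remission rate and recurrence rate of HSPN".
- **Secondary outcomes (section 2.5.2).** Symptom improvement and adverse events. On the scoring: "Each symptom or sign will be given a score, and the sum of all scores will be recorded in Table 1".
- **Time-to-event model (section 2.9).** Cox regression, for "associations between baseline risk factors and HSPN incidence, hazards ratios will be computed using the Cox proportional hazard regression models".
- **Group comparison (section 2.9).** "Comparisons between the groups will be conducted using an analysis of covariance (ANCOVA) with the baseline as the covariate". The sentence names no outcome.
- **Efficacy (section 2.9).** "For efficacy analysis, changes from the baseline to the endpoint of treatment in scores will be tested with repeated measured analysis of variance (ANOVA").
- **Other tests (section 2.9).** t and Mann–Whitney tests for baseline differences; paired t and Wilcoxon signed-rank tests for change within a group.

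Cohort membership follows the treatment received (section 2.2); nothing is randomised. The sample size (section 2.6) compares response rates of 53% and 40%.

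**The concern.** The methods that section 2.9 names do not meet the outcomes that section 2.5.1 names. The Cox model is pointed at the onset of a condition that is an entry requirement, and its stated purpose is to study baseline risk factors, not the effect of CHM. The analysis called efficacy concerns a secondary score and stops at the end of treatment, so it does not cover the 12-month follow-up, in which recurrence would largely be seen.

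The study hypothesises that CHM is effective and lowers recurrence. Followed as written, section 2.9 leads to an efficacy result on a symptom score and to no suitable adjusted comparison of remission or recurrence. Because treatment is not randomised, adjustment is central to any such comparison. Leaving the choice of primary model open also allows it to be made after the data are seen.

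**Working it through.** **1. The plan's own figure.** Section 2.6 gives 250 per group for 53% against 40%, two-sided alpha 0.05, 90% power. With the pooled formula and mean rate (0.53 + 0.40)/2 = 0.465:

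n = [1.960 × √(2 × 0.465 × 0.535) + 1.282 × √(0.53 × 0.47 + 0.40 × 0.60)]² / 0.13² ≈ 308 per group.

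So 250 does not reproduce; that is a separate matter, and this point does not depend on it. What matters here is that the sizing compares two proportions, which none of the methods in section 2.9 is designed to do.

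**2. The Cox sentence against the entry criterion.** A model for incident HSPN needs children who are free of HSPN at time zero. Planned enrolment is 600, and all 600 have HSPN at entry. The risk set for first onset is 600 − 600 = 0, so the event as worded cannot occur. If incidence is read as recurrence, events become possible, but the sentence still names baseline risk factors and not cohort.

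**3. The ANCOVA sentence, read as covering remission.** Let Y = 1 for remission and 0 otherwise, G = 1 for CHM and 0 for WM, and B = remission status at baseline. The model is

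Y = b0 + b1·G + b2·B.

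Assume that no child with active HSPN is in remission at entry, so that B = 0 for everyone. The design matrix then has 3 columns but rank 2, b2 cannot be estimated, and the estimate of b1 is the raw difference in proportions. At the planning rates that is 0.53 − 0.40 = 0.13. A check on simulated data with 250 per group gave rank 2 of 3 and a group coefficient of 0.164, equal to the raw difference in that sample. The specified adjustment therefore does nothing for remission. For recurrence, the article does not say what a baseline value would be.

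**4. The ANCOVA sentence, read as covering only scores.** The method is then appropriate to its outcome. The remaining methods map as follows:

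| Method in section 2.9 | What it addresses | Primary outcome? |
|---|---|---|
| Cox model | onset of HSPN by risk factor | no |
| t, Mann–Whitney | baseline differences | no |
| ANCOVA (this reading) | scores | no |
| Repeated-measures ANOVA | change in scores over treatment | no |
| Paired t, Wilcoxon | change within a cohort | no |

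Neither remission nor recurrence is matched to a method.

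**The case against.** The strongest reply is that this is a condensed article, and that a full analysis plan may set out the primary analyses. That stands as far as silence goes: if ANCOVA is meant only for scores, the lack of a method for remission and recurrence would not by itself be a fault. It does not excuse the Cox sentence, which states a target that the entry criterion rules out, or the use of the efficacy label for a secondary score. A fuller plan that followed this text would inherit both.

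A reader might infer that the stated analyses cannot estimate either primary outcome. The documents do not support that. ANCOVA on a 0/1 outcome still returns a crude risk difference, and the article never says that ANCOVA is for remission or recurrence. The sentence sits directly before the score analysis, and a baseline covariate fits scores naturally.

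A reader might also infer that the trial was sized on both primary outcomes. Section 2.6 speaks only of response; equating it with remission is plausible but not stated, and no recurrence rate is given. Nor does the article call the primary outcomes binary; the word rate and the sizing imply it.

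Finally, incidence may be loose wording for new episodes after remission. The repair would then be a clarification, but the sentence would still need it, and cohort would still be missing.

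**Conclusion.** The point holds in this form. One stated rule is wrong as written: the Cox model addresses an event that none of the 600 children can newly have, and its stated purpose is not the CHM versus WM contrast. Beyond that, neither of the two primary outcomes is given a suitable adjusted between-cohort analysis. Either ANCOVA applies and its baseline term is empty for remission, or it does not apply and no method is named.

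This rests on a literal reading of the Cox sentence, on remission and recurrence being event-type outcomes, and on no child being in remission at entry. The effect on the eventual recurrence estimate cannot be put in figures, because the article gives no recurrence rate or hazard ratio.

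**What to change.** In section 2.9:

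1. **Recurrence.** Replace HSPN incidence in the Cox sentence with HSPN recurrence over follow-up, with cohort (CHM versus WM) as the exposure, adjusted for the baseline characteristics already collected. State who is at risk and the time origin.
2. **All enrolled children.** Timing recurrence from remission keeps only children who remit, which selects on a post-baseline outcome that treatment may affect. So also report a comparison in everyone enrolled, for example remission sustained without recurrence to the end of follow-up.
3. **Remission.** Compare the proportion between cohorts by logistic regression adjusted for the same characteristics. Report an odds ratio and a risk difference standardised over the observed covariates, with 95% confidence intervals, at the time point that the sponsor assigns to remission.
4. **Scores.** Limit ANCOVA and repeated-measures ANOVA to the secondary symptom scores.

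The cost is a little more analysis work. No extra visits are needed, but remission and recurrence dates must be derived from the two-weekly and monthly visits, so they are known only to within a visit interval. Adjustment deals only with the characteristics that were measured.
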